**Measures for intervention group only**:

1) Behavioral tracking: Data from tracking through the *Fit After Baby* app will be analyzed to assess adherence to the program, including weekly weigh-ins (via provided scale), days with recorded physical activity data (transmitted by wearing Fitbit (provided), recorded real-time in the app, and/or manual entry), and days with dietary intake logged (via Fitbit app).

2) Engagement: We will collect data on 1) number of days using the app, 2) responses to prompts, 3) points and badges earned, and 4) number of interactions with lifestyle coach.

**Focus Groups:**

Subjects will be asked to attend a 1-2 hour focus groups via virtual zoom meeting. The groups will consist of up to 8 participants. There will be up to 8 sessions, each lasting no longer than 2 hours. They will be encouraged to respond to the facilitators’ questions and to each other’s comments on topics such as: barriers and facilitators to adoption and engagement of the Fit After Baby program. Participants will be recruited from the pool of participants who were involved in the FAB intervention group. Research staff will utilize a COMIRB approved focus group discussion guide to conduct the focus groups. Subjects will be allowed to take breaks as necessary. Participants will receive a $50 gift card as compensation for taking the time to come in person to provide us with their additional feedback. Group zoom sessions will be recorded and recordings will be stored on a secure server at the University of Colorado.

The patient re-consent process will be conducted using a REDCap-based electronic consent form. The consent form has been developed in REDCap, a secure, web-based, HIPAA-compliant, data collection platform with a user management system allowing project owners to grant and control varying levels of access to data collection instruments and data (e.g. read only, de-identified-only data views) for other users. Consent forms signed in RedCap will be converted to PDF and uploaded in the participants EMR per protocol.

Patient signatures will be obtained using a types signature. Upon completion of the consent, patients will be provided with a copy of their version of the consent document by allowing them to download a PDF of their consent form. The option to have the consent printed and mailed to participant by study staff will be available.

**Statistical Analysis**: The analysis for the primary outcomes will be intent-to-treat, using longitudinal mixed methods to account for loss to follow-up and censored participants. Due to the longitudinal nature of this study, we will assess the change in weight from the 6-week study visit to weight at 6 and 12 months by a mixed model analysis with an exchangeable correlation structure and adjustment for weight gain during pregnancy, and breastfeeding (a mediating effect). Within this model, we can further assess differences in weight between various time points by contrasts. We will also compare the delta weight prepregnancy to 6 and 12 months postpartum in the intervention group to the control group using a multivariate regression model, adjusting for age and race. Secondary clinical outcomes will be compared between groups by a generalized linear mixed model analysis, similar to the primary outcome analysis. When necessary, adjustment for multiple comparisons will be made. We will assess reach, effectiveness, and adoption per the RE-AIM model to prepare for a pragmatic trial (Table 2). We will use content-based analysis on focus group data to assess perceived barriers and facilitators to success of the intervention.

**Anticipated results**: Primary outcome: We expect that women who participate in the *Fit After Baby* program will demonstrate increased weight loss in the postpartum year vs. the Text4Baby control group. Secondary outcomes**:** We expect an improvement in cardiometabolic risk factors among women randomized to the Fit After Baby program. We anticipate that increased engagement and satisfaction will be associated with increased weight loss. We expect that decreased caloric intake relative to expenditure and increased physical activity will help to mediate weight loss. We anticipate that postpartum depression may interfere with weight loss as it will decrease engagement with the program, and appetite and sleep may also moderate weight loss.

| **Table 2: Relevant RE-AIM Outcomes** | **Measures/Data Source** | |
| --- | --- | --- |
| **REACH** | | |
| 1) Proportion of approached women agreeing to participate  2) Proportion of recruited women initiating program | | 1) Recruitment data  2) App usage data |
| **EFFECTIVENESS** | | |
| 1) Postpartum weight loss  2) Change in physical activity  3) Change in dietary intake | | 1) Change in weight from baseline and pre-pregnancy weight to 6 and 12 months postpartum  2) Change physical activity assessed by modified PPAQ  3) Change in diet assessed by 24-hour recall |
| **ADOPTION** | | |
| 1) Engagement with app and lifestyle coach  2) Acceptability and perceived barriers to success of intervention | | 1) Usage data from app (daily use, weight, diet, physical activity tracking, responses to prompts, points earned); number of interactions with lifestyle coach  2) Satisfaction; Participant focus group data |

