**5.5 Treatment assignment and randomization:**

At their first study visit (approximately 6 weeks postpartum), subjects will be randomized into either:

1. Text4Baby Group: 3 study visits (6 weeks, 6 months, 12 months) OR

2. Fit After Baby mHealth Intervention Group: 3 study visits (6 weeks, 6 months, 12 months) AND interaction with the Fit After Baby mHealth program and lifestyle coach

We will randomize in a 2:1 ratio favoring the intervention arm so that we can collect the maximal amount of data from users of the mobile application. This is important because we are collecting data about use of the mobile application in addition to the primary outcome for efficacy. Having more data on actual users will allow us to be more competitive for a future R01 submission emphasizing dissemination and implementation. We have improved the power of the study by adding subjects. Improving the power of the study will increase our likelihood of finding a true difference, which will in turn improve our ability to be competitive for a future R01 application. We will use a computer program to randomize subjects that will generate random treatment assignments using a permuted block scheme with randomly varying block sizes. We will schedule subjects as closely as possible to the 6 week, 6 month, 12 month dates. However, given potential scheduling conflicts with subjects at the clinics, we will allow a window of flexibility of 4-16 weeks postpartum for the 6-week visit. We will also allow one month before and after the 6-month and 12-month visits. After the trial, we will conduct focus groups with participants (2-4 focus groups, 5-8 per group) to assess barriers and facilitators to adoption and engagement of the Fit After Baby program.

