2) Lifestyle CoachA registered dietitian (RD) with training in patient-centered counseling techniques will work with the participants to help them set and achieve goals. The lifestyle coach will provide feedback, advice, and support through the *Fit After Baby* app, and via text messages and email messages. She will prepare to answer questions related to content for each week, how to use the app, and be available to answer any other questions the participant may want answered.

A study physician trained in patient centered counseling will periodically review email and text interactions, as well as notes from phone calls, to ensure adherence to these techniques. The coach and study physician will view progress of participants through a dedicated portal via an android coaching app where they can track diet, physical activity, weight, and progress towards individualized goals.

After a subject has completed the 12 month visit, we will send results of fasting glucose, lipid profile, hsCRP, HbA1c, and TSH from all study visits. The results will be accompanied by a letter from the study physician.

For women who completed their 6-week visit but do not complete their 6 or 12 month visits, we will attempt to reach them by phone, text, email, and/or mail. Additionally, during the consent process, we will get permission from subjects to contact a family member or friend if we are having trouble getting in touch with the subject at any point in the study.

Study Outcomes:

The primary outcomes are change in weight from baseline to 6 months and to 1 year postpartum (exit study visit), and change in weight from self-reported pre-pregnancy weight to one year postpartum.

Secondary outcomes**:** We will assess engagement and satisfaction with the program as potential mediators, defined as use of the app, adherence to self-monitoring of weight, diet, and physical activity, and interactions with the lifestyle coach. To assess changes in cardiometabolic risk factors we will obtain: blood pressure, waist circumference, and biomarkers at baseline, 6 months, and 12 months. We recognize that some of these measurements will be elevated in the postpartum state, however we hypothesize that we will see a greater change among women randomized to the intervention program. We will also assess sleep adequacy and appetite using scales embedded in the app and also sleep data from the Fitbit.

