Recruitment targets and power calculation: We plan to recruit at least 7 participants per month, with a goal of consenting 140 subjects to account for recruitment yield of 50-70%. After 2 years we should have data from 81 participants at one year postpartum. With 54 subjects in the intervention group and 27 subjects in the control group, a 2-sample t-test controlling for baseline weight will have at least 87% power to detect a 4.2 kg difference between groups in 12 month weight change (the 4.2 kg difference with a pooled standard deviation of 5.7 kg was observed in the Balance after Baby RCT). This is adequate power for a pilot study designed to establish the foundation for a subsequent larger pragmatic trial of the *Fit After Baby* program.

+Structured interviews

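### The exchangeable correlation fixed for the primary weight model can understate the 12-month standard error; type I error would be about 11% if successive weight changes are uncorrelated

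*Protocol*

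**What the plan says.** Under Study Outcomes: "The primary outcomes are change in weight from baseline to 6 months and to 1 year postpartum". A further primary outcome is the change from pre-pregnancy weight to one year.

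The Statistical Analysis paragraph analyses the change from the 6-week visit by a "mixed model analysis with an exchangeable correlation structure", and adds: "Within this model, we can further assess differences in weight between various time points by contrasts". It names no other covariance structure and does not say how standard errors are estimated. The pre-pregnancy comparison goes to a separate regression.

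Section 5.5 sets visits at 6 weeks, 6 months and 12 months postpartum, with "a window of flexibility of 4-16 weeks postpartum for the 6-week visit" and one month either side for the later two. The power paragraph reads "With 54 subjects in the intervention group and 27 subjects in the control group", and claims "at least 87% power to detect a 4.2 kg difference between groups in 12 month weight change", using a pooled SD of 5.7 kg. That SD is the only variability figure given for weight change.

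**The concern.** An exchangeable structure with one common variance makes the change from 6 weeks to 6 months, from 6 to 12 months and from 6 weeks to 12 months equally variable. The intervals are about 4.6, 6.0 and 10.6 months. Serial body weights are usually least alike at the visits furthest apart, so the longest change is likely to be the most variable. The model then averages short and long intervals and assigns the average to each.

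Exchangeability also requires successive changes to be negatively correlated, at exactly -0.5, so that women who lose early tend to regain. The protocol's Background (part C) points towards persistence: weight still held at 6 to 12 months postpartum tends to stay.

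At stake are the p-value and confidence interval for the powered 12-month comparison, which are meant to inform a larger trial. The visit windows add to the doubt: the first interval can be as short as about 1.3 months (16 weeks to 5 months).

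**Working it through.** **Inputs from the protocol.** 54 and 27 women; SD of 12-month change 5.7 kg; difference 4.2 kg; visits at 6 weeks, 6 and 12 months.

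**Assumed, because not given.** Two-sided alpha 0.05; the variances of the 6-month change (V6) and of the 6-to-12-month change (Vb) relative to the 12-month change (V12); model-based standard errors; a common variance.

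**1. Reproduce the plan's power.** True SE = 5.7 × √(1/54 + 1/27) = 1.34 kg, and 4.2/1.34 = 3.13. Power is 87.0% (noncentral t, 79 df) or 87.8% (normal). The stated 87% is correct.

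**2. What the model reports.** With complete data, the exchangeable model gives each change the variance (V6 + Vb + V12)/3. Hence

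- SE ratio at 12 months, R = √[((V6 + Vb + V12)/3)/V12]
- type I error = 2 × (1 − Φ(1.96 × R))
- at 6 months the same formula applies with V6 in the denominator.

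**3. Uncorrelated successive changes.** Then V6 + Vb = V12, so R = √(2/3) = 0.816, however the variance splits between the two intervals. Model SE = 0.816 × 1.34 = 1.10 kg. Type I error = 2 × (1 − Φ(1.600)) = 11.0%. If variance is also proportional to time, V6/V12 = 4.62/10.62 = 0.435. The 6-month ratio is then √(0.667/0.435) = 1.24 and its type I error is 1.5%.

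**4. Other assumptions.**

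| Assumption | V6/V12 | Vb/V12 | R | 12-month type I |
|---|---|---|---|---|
| Visit correlations 0.92 (6 wk–6 mo), 0.95 (6–12 mo), 0.94 (6 wk–12 mo) | 1.33 | 0.83 | 1.027 | 4.4% |
| Exchangeability true | 1 | 1 | 1.000 | 5.0% |
| Unequal variances with V6 + Vb = 2 × V12 | 1.2 | 0.8 | 1.000 | 5.0% |
| 6-month change as variable as 12-month, later change half | 1 | 0.5 | 0.913 | 7.4% |
| Time-proportional, half of V12 is visit noise | 0.72 | 0.78 | 0.913 | 7.4% |
| Time-proportional, a quarter is noise | 0.58 | 0.67 | 0.866 | 9.0% |
| Time-proportional, no noise | 0.435 | 0.565 | 0.816 | 11.0% |
| Linear divergence | 0.19 | 0.32 | 0.709 | 16.5% |

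**5. Two change scores as the response.** If only the 6- and 12-month changes are modelled with a common variance, R = √[(0.435 + 1)/2] = 0.847 and the type I error is 9.7%.

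**6. Simulation.** REML compound-symmetry fits with 54 and 27 women, no dropout, and 1,500 or 4,000 replicates gave 12-month type I errors of:

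- 5.3–5.6% when the data are truly exchangeable
- 9.5% with time-proportional variance plus a quarter noise
- 11.4–11.6% with time-proportional variance and no noise; mean model SE about 1.10 kg against an empirical 1.36 kg, and about 1.6% type I error at 6 months.

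With 20% dropout the last case gave 10.1%. With sandwich standard errors and no dropout it gave about 6%.

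**The case against.** The protocol supplies no between-visit correlation and no SD for the shorter intervals. A reader might infer that the chosen structure doubles the false-positive rate as a matter of course. The documents do not support that: the doubling comes from an assumed correlation pattern, and the table includes patterns with no inflation or a slightly conservative test. Nor does 5% require all three changes to be equally variable; V6 + Vb = 2 × V12 is enough. Time-proportional variance may also fit poorly here, because the intervention is intensive for 12 weeks and then eases, so change could come early. This objection stands and limits the size of the claim.

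The paragraph can also be read as modelling two change scores. With two occasions there is only one correlation, so exchangeability restricts nothing; only a common variance, which the text does not state, could bias the standard error. This partly stands. The sentence "we can further assess differences in weight between various time points by contrasts" fits a model of the visit weights better, and the two-score reading with common variance still gives about 10%.

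The standard-error estimator is not stated and may properly be left to the SAP. That silence is not a fault, and robust standard errors would remove most of the problem. The correlation structure, however, is not left open; the protocol chooses it.

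Finally, this is a pilot (section 5.1), and the pre-pregnancy comparison uses a separate regression that is unaffected. Both points lower the severity.

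**Conclusion.** The point holds conditionally. The protocol commits its primary model to a structure that, under the usual common variance and model-based standard errors, is right for the 12-month contrast only if V6 + Vb happens to equal 2 × V12. If successive weight changes are uncorrelated, the 12-month standard error is about 1.10 kg instead of 1.34 kg and the type I error is about 11% (about 10% with two change scores). With time-proportional variance the 6-month contrast errs the other way, at about 1.5%. Across the assumptions tried, the 12-month figure runs from about 4.4% to about 16%.

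It would be wrong to conclude that the power calculation is in error, since it reproduces. Nor has it been shown that the structure causes further bias through missing visits: the 20% dropout run gave much the same inflation. Severity: should-fix, because an avoidable and unsupported assumption governs the error rate of the powered comparison.

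**What to change.** In the Statistical Analysis paragraph, replace the exchangeable structure with an unstructured covariance across the three visits, fitted by REML with Kenward-Roger degrees of freedom. State a fallback in case it does not converge: a heterogeneous autoregressive or Toeplitz structure, or a simpler structure with robust (sandwich) standard errors. Say also whether the response is the three weights or the two change scores.

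The cost is a change of wording and four more covariance parameters (six instead of two, from up to 81 × 3 = 243 weights). The 12-month interval may be slightly wider. The analysis remains valid if exchangeability turns out to be true. Data collection and sample size do not change.

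### The power statement assumes a test adjusted for baseline weight, but the primary mixed model analyses change without 6-week weight as a covariate; aligning the two brings a small gain at almost no cost

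*Protocol*

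**What the plan says.** The paragraph on recruitment targets and power in Protocol section 5.6 describes the powered comparison: "a 2-sample t-test controlling for baseline weight will have at least 87% power to detect a 4.2 kg difference" in 12-month weight change. The group sizes are given by "With 54 subjects in the intervention group and 27 subjects in the control group", in line with the 2:1 allocation in section 5.5. The source of the effect and its spread is that "the 4.2 kg difference with a pooled standard deviation of 5.7 kg was observed in the Balance after Baby RCT". The paragraph does not say whether 5.7 kg is the SD of raw change or a residual SD after adjustment for baseline.

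The Statistical Analysis paragraph gives the primary outcome and model: "we will assess the change in weight from the 6-week study visit to weight at 6 and 12 months by a mixed model analysis". The model is specified as a "mixed model analysis with an exchangeable correlation structure and adjustment for weight gain during pregnancy, and breastfeeding", so two adjustments are named. The paragraph allows contrasts between time points. It does not name 6-week weight as a covariate. It also does not say whether the 6-week visit is one of the responses or whether the arms share one baseline mean. The separate regression for change from pre-pregnancy weight lists only age and race.

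**The concern.** The two paragraphs describe different comparisons. A test that controls for baseline weight estimates the slope of later weight on baseline weight from the data. A change score fixes that slope at 1. The two coincide only if the true slope is 1.

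Three things are at stake, all modest:

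- **Consistency.** The analysis that was powered and the analysis that is planned should be the same. A reader cannot tell which estimate is primary, and in a trial of 81 the two can differ.
- **Precision.** Weight is measured at the visit at which women are randomised, so adjustment is available at no cost in data.
- **Chance imbalance.** With arms of 54 and 27, a chance difference in baseline weight carries partly into a change contrast. Adjustment removes that carry-over.

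**Working it through.** **Inputs from the protocol:** 54 and 27 women, difference 4.2 kg, SD 5.7 kg.

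**Assumptions:** two-sided alpha 0.05, because the power paragraph states none. The SD of body weight is not given, so 12, 15 and 18 kg are shown. Equal SDs at baseline and 12 months are assumed in steps 2 to 5 and relaxed in step 6.

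**1. The stated power.** SE = 5.7 × √(1/27 + 1/54) = 5.7 × 0.2357 = 1.344 kg. The noncentrality is 4.2/1.344 = 3.13 on 79 degrees of freedom, which gives 87.0%. The protocol's figure reproduces with no variance reduction for baseline.

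**2. Does putting baseline among the responses already adjust for it?** Under exchangeable covariance and complete data, with a free baseline mean in each arm, the generalised least squares SE of the 12-month change contrast is 1.344 kg at all three SDs. That is the t-test's SE. Only a baseline covariate or a common baseline mean lowers it.

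**3. Gain from adjustment, if 5.7 kg is the SD of unadjusted change.** The correlation is ρ = 1 − 5.7²/(2 × SD²). The ratio of adjusted to change-score variance is (1 + ρ)/2. Power uses 78 degrees of freedom.

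| Weight SD (kg) | ρ | Variance ratio | SE (kg) | Power |
|---|---|---|---|---|
| 12 | 0.887 | 0.944 | 1.305 | 88.8% |
| 15 | 0.928 | 0.964 | 1.319 | 88.2% |
| 18 | 0.950 | 0.975 | 1.327 | 87.8% |

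The saving is 5.6%, 3.6% and 2.5% of variance, or about 1 to 2 power points.

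**4. If 5.7 kg is already a baseline-adjusted SD.** Then 5.7 = SD × √(1 − ρ²), and the SD of unadjusted change is SD × √(2(1 − ρ)).

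| Weight SD (kg) | ρ | SD of change (kg) | Power of unadjusted change |
|---|---|---|---|
| 12 | 0.880 | 5.88 | 84.9% |
| 15 | 0.925 | 5.81 | 85.8% |
| 18 | 0.949 | 5.77 | 86.2% |

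**5. Chance imbalance at SD 15 kg.** The SE of the baseline difference is 15 × 0.2357 = 3.54 kg. A one-SE imbalance shifts the change contrast by (1 − 0.9278) × 3.54 = 0.26 kg, about 0.2 of its own SE (0.26/1.344).

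**6. Unequal SDs.** Take a baseline SD of 15 kg and a change SD of 5.7 kg. The slope of 12-month on baseline weight equals 1 when the 12-month variance is 15² + 5.7² = 257.5, an SD of 16.05 kg or 7% above baseline. The gain is then zero. At 5% above (15.75 kg) the variance ratio is 0.997 and power about 87.1%.

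**The case against.** The strongest reply is that baseline weight is not missing. It is subtracted in the outcome, and the allowance for contrasts between time points is compatible with baseline as a response under a common mean, which would meet the power paragraph's wording. Details of that kind are often left to a statistical analysis plan, which is not shown. Powering on a simpler test than the model finally fitted is also common, and this is a pilot.

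Much of this stands. It would be wrong to say that the model ignores baseline weight. But the protocol is not silent: it names the covariates of the primary model and, separately, an adjustment for the powered test, and the two lists differ. Step 2 shows that baseline among the responses does not adjust unless the means are constrained, and the protocol does not say that they are.

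The size of the gain is also open to challenge. It depends on SDs that the documents do not give and on equal variances. BMI is restricted at entry but not at 12 months, so a larger spread at 12 months is plausible, and step 6 shows how quickly the gain then disappears. The model already adjusts for pregnancy weight gain, so the increment over the planned model is unknown. These points stand, and the lower end of the range must be zero.

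A reader might infer that the 87% is an error, or that it is by definition the unadjusted value. The documents support neither. The power is stated as a minimum, which both the unadjusted 87.0% and the adjusted values in step 3 satisfy. Whether 5.7 kg is adjusted is not stated. A reader might also infer bias, but randomisation keeps the change contrast unbiased; an imbalance in one trial moves the estimate, not its expectation.

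**Conclusion.** The mismatch is real: the power paragraph names a baseline-adjusted test, and the primary model as written is an analysis of change without that adjustment. The consequence is small. Over an assumed weight SD of 12 to 18 kg, adjustment saves 0 to about 6% of variance and adds 0 to about 2 power points. If 5.7 kg is an adjusted SD, the planned change analysis falls 1 to 2 points short of the stated minimum. Both results ignore any variance explained by the covariates already listed. This is a low-cost improvement and a clarification, not a flaw that threatens the trial's conclusions.

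**What to change.** In the Statistical Analysis paragraph, model weight at 6 and 12 months with arm, visit, arm-by-visit, 6-week weight and 6-week weight by visit. Alternatively, keep the 6-week weight among the responses with one common mean for both arms. Take the 12-month arm contrast from that model.

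In the power paragraph, name that contrast as the powered one and state whether 5.7 kg is an adjusted or unadjusted SD of change. The 87% should not be labelled an unadjusted value until this has been checked against the source trial.

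The cost is about one sentence in each paragraph and about one degree of freedom for the 12-month contrast. No new data are needed.
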